### Outcome measures

The primary outcome measure is the incidence of functional impairment as measured by the difference in function after 2 years of follow-up between intervention and usual care groups, assessed by changes in summary ordinal score on the SPPB test ≥1. Data from a previous study have shown that one point is the minimum change in the SPPB test that can be considered clinically significant [26]. Secondary outcome measures are listed in Table 2.

**Table 2 T2:** Primary and secondary outcome measures

**Outcome measure**	**Definition**
Primary	The difference in function after 2 years of follow-up between intervention and usual care groups, according to changes in summary ordinal score on the SPPB test ≥1 [26].
Secondary	a) Barthel ADL index [13] and b) Lawton IADL scale [27].
	c) Quality of life, as measured by using the EuroQoL index, EQ-5D-5 L [28].
	d) Economic costs/health care expenditure due to diabetes and its impact on disability and quality of life, using an economic model embracing the direct health-related costs (in-subject, out-subject, pharmaceutical), formal care costs (home care, respite care, day centres), and the informal care costs (carer).
	e) Episodes of symptomatic hypoglycaemia (that is, a recorded blood sugar <4 mmol/L, or symptoms or signs attributed to low blood sugar and responding to appropriate treatment).
	f) Episodes of hospital admission (that is, any admission involving an overnight stay).
	g) Episodes of permanent institutionalisation (that is, permanent move to any care setting other than the subject’s own home, where paid staff are available to provide care if needed at any time during the day or night).
	h) Burden of the carer, as assessed by the Modified Caregiver Strain Index (MCSI) [29].
	i) Mortality.

ADL, activities of daily living; IADL, instrumental activities of daily living; MCSI, Modified Caregiver Strain Index; SPPB, short physical performance battery.

#### Economic assessments

The main aim of the economic assessment is to estimate the incremental cost-effectiveness ratio of the multi-modal intervention in frail and pre-frail subjects aged ≥70 years with type 2 diabetes in comparison with usual best clinical practice. Three types of cost will be assessed through a comparative analysis of the alternative courses of action in terms of both their financial costs and their health outcomes: 1) direct health care costs, these costs are related to in-subject and out-subject treatment, and medicines; 2) formal care (mainly social services) costs, this includes those services that involve public or private funding, including the use of a day centre, nursing home, residential care, home support services, and personal alarm system; and 3) informal care costs, informal support includes the different types of non-paid support provided by relatives and friends as a result of the subject’s disability.

### Safety assessments

All co-existing diseases or conditions will be treated in accordance with prevailing medical practice. All medications (prescription and over-the-counter) that started before screening may be continued during the study and will be recorded as concomitant therapy on the electronic case report form (eCRF). Medications for any conditions that may arise after screening, or for worsening of an existing condition, will be allowed and recorded on the eCRF; the condition will be reported as an adverse event. Standard safety data on adverse drug reactions will be collected and reported.

### Power and sample size

The sample size per group (intervention and usual care group) will be 859 subjects. This sample size has been calculated according to the following assumptions: a yearly incidence of functional impairment in frail/pre-frail subjects (main variable) of 30% [30], accumulated incidence of functional impairment in 2 years of intervention of 51% (assuming a constant 30% incidence rate year on year), an intervention effect size of 20%, a z statistic to compare the proportions of dichotomous variables (as the statistical test), a two-tailed α = 0.05, a two-tailed 1-β = 0.8, an intra-cluster coefficient correlation of 0.05, an average cluster size of 15, and a coefficient of variation cluster size of 0.25 [31,32]. Assuming a 20% loss of subjects during follow-up, the final sample size will be 1,718 subjects.

### Statistical analysis

The primary analysis will compare the odds of developing functional impairment in the intervention group with the usual care group, controlling for baseline function, using a hierarchical logistic regression model with subjects nested within trial sites. This will be an intention-to-treat analysis controlling for subject characteristics, such as subject age, gender, and comorbidities. The groups will be compared in terms of odds ratios and relative risks.

Secondary outcome variables include: 1) quality of life as measured by the quality of life measurement tool EQ-5D-5 L (EuroQoL, Rotterdam, Netherlands), which will be used in the economic evaluation; 2) hospital admission, mortality, and permanent institutionalisation, which will be investigated using hierarchical logistic regression models, and the results summarised using odds ratios and relative risks. If there are multiple outcomes per subject (for example hospital admission), Poisson regression may be used. Hierarchical survival analysis may also be used to model the time to first event; 3) carer burden and quality of life, which will be addressed using hierarchical regression models; and 4) validation of the Audit of Diabetes-Dependent Quality of Life (ADDQoL) senior scale [33], including measuring internal consistency (using Cronbach’s alpha) and establishing convergent and divergent validity (by comparing subject characteristics expected and not expected to be related with ADDQoL senior and ADDQoL senior scores). Floor and ceiling effects will be investigated. Correlation analysis will be conducted to identify whether the ADDQoL senior scale correlates with the other measures of function used in this study. Test re-test reliability will also be estimated (the ADDQoL senior will be administered at weeks 0, 26, 52, 78, and 104).

All analyses, except for the economic assessment, will be run by team members at Cardiff University in collaboration with the study and sub-study teams. The economic analysis will be performed by team members from Universidad Castilla-La Mancha (Ciudad Real, Spain). Standard imputation methods (for example mean value imputation, last observation carried forward) will be used to impute missing data depending on the pattern of missing data. Dropout due to death is a possibility in this study population. A sensitivity analysis will be run in which dropouts due to death will be assigned the minimum function score. Joint modelling of function and dropout due to death will also be explored. A causal adjusted complier analysis will be used to estimate the treatment effect observed in those subjects who complied with the intervention. Survival analysis naturally deals with censoring, which will help minimise the effect of dropout in the secondary analyses. No interim analysis is planned and is not accounted for in the sample size calculation. An ethics independent external advisory committee will be formed and will meet at least three times during the course of the study to evaluate its progress, the safety data, the critical efficacy endpoints, and will make any recommendations to the sponsor and the steering committee whether to continue, modify, or stop the study.

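### The optional Poisson model for repeated hospital admissions carries no site effect and no allowance for overdispersion; used as written, its intervals would be too narrow

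*Protocol article*

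**What the plan says.** Table 2 (Outcome measures) counts admissions as episodes: "Episodes of hospital admission (that is, any admission involving an overnight stay". A subject can therefore contribute several.

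The Statistical analysis section names three models for outcomes of this kind:

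- The main one covers "hospital admission, mortality, and permanent institutionalisation, which will be investigated using hierarchical logistic regression models".
- For repeated events: "If there are multiple outcomes per subject (for example hospital admission), Poisson regression may be used".
- For timing: "Hierarchical survival analysis may also be used to model the time to first event".

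The primary model is also hierarchical, with subjects nested in sites, as are the models for carer burden and quality of life.

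On loss to follow-up the same section says: "Survival analysis naturally deals with censoring, which will help minimise the effect of dropout in the secondary analyses". Shortly before that it notes: "Dropout due to death is a possibility in this study population". Two remedies for death follow: "A sensitivity analysis will be run in which dropouts due to death will be assigned the minimum function score" and "Joint modelling of function and dropout due to death will also be explored". Both concern the function score.

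**The concern.** Logistic regression reduces admissions to any or none. Poisson regression is the only named model that uses the episode count as Table 2 defines it. It is also the only model in the account of the primary and secondary between-arm comparisons that is not called hierarchical, although whole sites are allocated. It sits between two models that are.

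Two sources of variance are then left out. Subjects at one site share staff, local practice and admission thresholds, so their counts are correlated. Within a site, admissions in frail older people tend to concentrate in a minority of subjects, so the variance exceeds the mean, while the Poisson model sets the two equal. Each omission shrinks standard errors and p-values for a listed secondary outcome.

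The censoring sentence raises a smaller matter. Censoring is harmless only if it is unrelated to the event. Death prevents a later admission or move to institutional care, and the stated remedies for death do not reach those outcomes.

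**Working it through.** **1. The plan's design effect.** Inputs from Power and sample size: ICC 0.05, mean cluster size 15, coefficient of variation of cluster size 0.25.

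DE = 1 + ((1 + 0.25²) × 15 − 1) × 0.05 = 1 + 14.9375 × 0.05 = 1.747.

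This is the value the plan used. Two-year incidence is 1 − 0.70² = 0.51, and a 20% relative reduction gives 0.408. A two-sided 5% test with 80% power and continuity correction needs 393 per group. Then 393 × 1.747 = 686.5, and 686.5 / 0.80 = 858.2, rounded up to 859, the stated figure.

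**2. Error rate when variance is understated.** If the true variance is V times the model variance, a nominal two-sided 5% test rejects with probability 2 × (1 − Φ(1.96/√V)).

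- *Site ignored, no overdispersion.* V = 1.747, √V = 1.32, error rate 13.8%. The ICC is stated for functional impairment; applying it to admissions is an assumption. With ICC 0.02, V = 1 + 14.9375 × 0.02 = 1.299 and the rate is 8.5%. With ICC 0.01, V = 1.149 and the rate is 6.8%.
- *Overdispersion only.* V is the variance-to-mean ratio φ. The documents give no admission rate or dispersion, so φ is assumed.
- *Both.* V = φ × 1.747, with the ICC taken on the total variance of the count.

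| φ (assumed) | Overdispersion only | With site also ignored |
|---|---|---|
| 1.5 | 11.0% | 22.6% |
| 2 | 16.6% | 29.4% |
| 3 | 25.8% | 39.2% |

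At φ = 2 alone the true standard error is √2 = 1.41 times the Poisson one.

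**3. Plausibility of φ.** If subjects' rates follow a gamma distribution with dispersion k, then φ = 1 + mean × k. A mean of 0.3 to 1.2 admissions over two years with k from 0.5 to 2 (all assumed) gives φ from 1.15 to 3.4 and error rates of 6.8% to 28.8%. A ratio of 2 corresponds, for example, to mean 0.5 and k = 2.

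**4. Simulation.** The set-up was 118 sites of about 14.5 subjects, mean 0.5 to 0.8, k 0.5 to 1, and log-site variance 0.1 (the mean, k and site variance are assumed). Poisson with model-based standard errors rejected about 18% to 27% of the time under the null. Cluster-robust variance rejected about 5% to 6%.

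**5. Death as a competing event.** Assume constant hazards: admission 0.25 per year, death 0.05 to 0.12 per year (two-year mortality 9.5% to 21%).

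- One minus Kaplan–Meier at two years: 1 − exp(−0.5) = 39.3%.
- Cumulative incidence: 0.25/0.30 × (1 − exp(−0.60)) = 37.6%, and 0.25/0.37 × (1 − exp(−0.74)) = 35.3%.

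So absolute risk would be overstated by about 2 to 4 points.

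**The case against.** The strongest reply is that nothing here is fixed. Poisson regression is permitted rather than prescribed, beside a committed hierarchical logistic analysis of the same outcome. The text does not exclude a site effect, robust variance or a negative binomial model, and an article condenses a fuller protocol whose analysis plan may settle the matter. The dispersion figures are assumed and the ICC belongs to another outcome. All of this stands, and it makes the error rates conditional. It does not dispose of the point. The article does name a model for counts and, unlike its neighbours, leaves the site structure out; a better model can be named at almost no cost.

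Four stronger readings are tempting and are not supported:

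- *Admissions will be analysed by plain Poisson regression.* The wording is optional, and plainness is an inference from what the sentence leaves out.
- *Survival analysis is claimed to deal with dropout by itself.* The text claims only that it helps to reduce the effect.
- *The survival intervals are also too narrow.* That model is hierarchical.
- *Death is ignored.* It is addressed for function, and mortality is an outcome in its own right. The gap is confined to admission and institutionalisation. Even there, a cause-specific hazard model properly censors at death, and the plan promises no Kaplan–Meier risks. The 2 to 4 points arise only if absolute risks are reported that way.

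**Conclusion.** The point holds as a conditional one about a secondary analysis. If the Poisson option is used as written, intervals for repeated admissions will be too narrow. The false-positive rate at nominal 5% would be about 13.8% from ignoring site alone, if the primary-outcome ICC carries over. It would be about 17% from overdispersion alone at an assumed ratio of 2 (11 to 26% for 1.5 to 3), and about 29% (23 to 39%) with both. The direction does not depend on the assumed values so long as counts are clustered or overdispersed; the size does.

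The censoring sentence is loosely worded rather than wrong. It needs its assumption stated, because the same section names death as a cause of dropout. The primary analysis, the hierarchical logistic and survival models and the 859 per group are untouched.

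**What to change.** Amend the Poisson sentence to say that any model for repeated events will:

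- be negative binomial, or otherwise robust to overdispersion;
- include a site random effect or use cluster-robust variance;
- carry an offset for log time at risk, ending at death or last contact.

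A site random intercept added to a Poisson model would not by itself cover variation between subjects within a site. Cluster-robust variance covers both sources.

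Qualify the censoring sentence: survival methods reduce the effect of dropout only where censoring is non-informative. Add that any absolute risk of first admission or institutionalisation will be reported as cumulative incidence with death as a competing event.

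The cost is a few lines of text and standard software. The downside is somewhat wider intervals for this outcome. No extra data or subjects are needed.

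### The only imputation methods named, mean value and last observation carried forward, would bias the SPPB endpoint if applied to it, and no sound method or sensitivity analysis is stated for dropout other than death

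*Protocol article*

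**What the plan says.** Under Statistical analysis, the protocol article says "Standard imputation methods (for example mean value imputation, last observation carried forward) will be used to impute missing data" and lets the pattern of missingness decide which. It does not say whether this concerns the outcome, the covariates or both.

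The same section gives deaths their own treatment: a sensitivity analysis that assigns the lowest function score, and exploratory joint modelling of function and death. It relies on censoring to limit the effect of dropout in the secondary analyses only. The complier analysis concerns adherence, not missing outcomes.

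Under Outcome measures, the primary endpoint is the incidence of functional impairment at 2 years, "assessed by changes in summary ordinal score on the SPPB test ≥1". Under Statistical analysis, it is compared by hierarchical logistic regression on an intention-to-treat basis. Under Power and sample size, impairment is assumed to arise at 30% a year and reach 51% at 2 years, and the loss allowance reads "Assuming a 20% loss of subjects during follow-up, the final sample size will be 1,718 subjects".

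**The concern.** The population is expected to decline, and the endpoint is a threshold on change from baseline. LOCF assumes that nothing happens after the last visit. A subject whose last SPPB is the baseline value gets a change of 0 and cannot be impaired. A subject last seen at year 1 keeps the year-1 risk. Mean imputation, if the quantity imputed is the mean change, gives all missing subjects the same value and hence the same classification. Both are single imputations, so the standard errors treat filled-in values as data.

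The distortion acts on the primary comparison. If dropout is the same in both arms, the effect is diluted. If it differs by arm, a difference in dropout becomes a difference in impairment. Differential dropout is plausible, because the trial is open and only the intervention arm attends supervised training and group sessions, repeated in year 2. The article gives no figure for it.

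**Working it through.** **Inputs (Power and sample size).** Yearly incidence 30%; two-year incidence 1 − 0.7² = 51%; effect 20%; loss 20%; two-sided α 0.05; power 0.80; intra-cluster correlation 0.05; mean cluster size 15; coefficient of variation of cluster size 0.25; 859 per arm. I read impairment as a loss of at least 1 SPPB point.

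**Reproducing the plan's sample size.** Reading the effect as relative, the intervention rate is 0.51 × 0.8 = 40.8%, a difference of 10.2 points. The two-proportion formula with continuity correction gives 393 per arm. The design effect is 1 + ((1 + 0.25²) × 15 − 1) × 0.05 = 1.747. Then 393 × 1.7469 = 686.5, rounded up to 687, and 687 / 0.8 = 858.75, rounded up to 859. This matches the plan exactly. An absolute 20-point effect gives only 207 to 228 per arm, so the relative reading is the one used.

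**LOCF formula.** Recorded rate = (1 − d) × (two-year risk) + d × (risk at last observation), where d is the proportion lost. Risk at last observation is 0 at baseline. At year 1 it is 0.30 in usual care and, with a constant yearly risk, 1 − √(1 − 0.408) = 0.2306 under intervention. Dropouts are taken to have the same underlying risk as completers. Rejection rates use a two-proportion z test with effective n = 859 / 1.7469 = 492 per arm, as an approximation to the hierarchical model.

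**Equal 20% loss, planned effect present.**
- Baseline carried: 0.8 × 0.51 = 0.408 against 0.8 × 0.408 = 0.3264; difference 8.2 points.
- Year-1 value carried: 0.408 + 0.2 × 0.30 = 0.468 against 0.3264 + 0.2 × 0.2306 = 0.3725; difference about 9.5 points.

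With no true effect and equal loss at equal times, the recorded rates are equal and type I error stays at 5%, apart from any understatement of the standard error.

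**No true effect, loss 15% usual care and 25% intervention (assumed).**

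| Value carried | Usual care | Intervention | False benefit | z | Type I error |
|---|---|---|---|---|---|
| All baseline | 0.85 × 0.51 = 0.4335 | 0.75 × 0.51 = 0.3825 | 5.1 points | 1.63 | 37% |
| Half year 1 | 0.4335 + 0.075 × 0.30 = 0.456 | 0.3825 + 0.125 × 0.30 = 0.420 | 3.6 points | 1.14 | 21% |
| All year 1 | 0.4335 + 0.15 × 0.30 = 0.4785 | 0.3825 + 0.25 × 0.30 = 0.4575 | 2.1 points | 0.66 | 10% |

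A wider assumed split of 10% and 30% gives 10.2 points (all baseline) to 4.2 points (all year 1), with type I error of 91% to 26%.

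**Planned effect present, loss 25% usual care and 15% intervention (assumed).**
- All baseline: 0.75 × 0.51 = 0.3825 against 0.85 × 0.408 = 0.3468; 3.6 points, power 0.21.
- All year 1: 0.3825 + 0.25 × 0.30 = 0.4575 against 0.3468 + 0.15 × 0.2306 = 0.3814; 7.6 points, power 0.68. Applying the 20% relative reduction at year 1 instead (0.24) gives 0.3468 + 0.036 = 0.3828, or 7.5 points.

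**Mean imputation of change.** Treat the integer SPPB change as a rounded normal variable, so that impairment means a latent change of −0.5 or lower. The mean is then −0.5 − SD × z(p). For an assumed SD of 1 to 3, 51% impaired implies a mean of −0.53 to −0.58, and 40.8% implies −0.27 to +0.20. All lie above −1, so every subject given the mean change is scored not impaired. If subjects who are not impaired average zero change, the mean reaches −1 only when the impaired lose on average 1 / 0.51 = 1.96 points in usual care or 1 / 0.408 = 2.45 under intervention. Every missing subject is then scored impaired.

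**With a valid method under missing at random.** The rates stay at 51% and 40.8%, type I error at 5%, and power at about 0.82 on 687 completers per arm.

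**The case against.** A reader might infer that the trial is bound to fill missing SPPB scores by these two methods. The text does not go that far. They are examples, the choice depends on the pattern found, and the full analysis plan is not shown. Nor is the outcome named: the model also adjusts for baseline characteristics, where mean imputation can be defended. What stands is that imputation is promised, both illustrations are single imputations, and nothing in the article covers non-death dropout in the primary analysis. That is a poor choice stated, not a detail left out.

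A reader might also infer that all dropouts would be scored as not impaired. That is true of LOCF only when the carried value precedes the decline; a subject already down a point stays impaired. The article gives no SPPB visit schedule. ADDQoL is collected at weeks 0, 26, 52, 78 and 104, so interim SPPB values are plausible and the milder figures may be nearer the truth. For mean imputation, it holds only if the mean change is imputed and lies above −1. If a mean follow-up score were imputed, the classification would vary with baseline.

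Finally, a reader might infer that a false positive is likely. The article gives one 20% loss for the whole trial and does not split it by arm or cause. Some of it may be deaths, which the minimum-score sensitivity analysis would address, though not in the primary analysis. The false benefit depends on dropout differing by arm in rate, timing or reason. With equal dropout the harm is dilution.

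**Conclusion.** The concern holds in limited form. If the named methods are applied to missing SPPB outcomes, LOCF records 0% to about 30% impairment among dropouts where the plan expects 51%, and a single mean change classifies them all alike. With equal 20% loss, LOCF leaves 8.2 to about 9.5 of the planned 10.2 points. Under an assumed 15% and 25% loss it gives a false benefit of 5.1 to 2.1 points and a type I error of about 37% to 10%. Under the reverse split about 3.6 to 7.5 points of the true effect remain.

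These figures rest on the plan's own incidence and clustering assumptions, on dropouts having the completers' risk, on the assumed splits, and on last values lying between baseline and year 1. The documents do not show that these methods are fixed for the endpoint or that dropout will be unequal.

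**What to change.** State that mean-value imputation and LOCF will not be used for missing SPPB outcomes. For SPPB missing for reasons other than death, use multilevel multiple imputation of the score, by arm and with a site random effect, from baseline SPPB, any interim SPPB and predictors of dropout. Then derive the binary endpoint in each completed data set and fit the planned hierarchical logistic model. Add a delta-adjusted sensitivity analysis for non-death dropout, in which imputed scores are shifted by stated amounts. Mean imputation may stay for baseline covariates.

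A repeated-measures mixed model on the SPPB score should not be offered as equivalent: it estimates a mean difference, whereas the planned primary analysis estimates the odds of impairment.

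The cost is a change of wording and modest extra programming. No new data are needed, and 859 per arm stands.
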